##### Implementation study

All patients with CKD in the intervention group will be invited to complete the survey. Also, patients with CKD and care providers in the intervention group will be invited and interviewed either face to face or by telephone for the process evaluation. We will use “purposive and convenience sampling” to ensure diversity (e.g., CKD stage age, gender) of our sample, especially when there are many patients who would like to join the interview study and choices concerning participation need to be made. If only a few patients indicate that they want to participate in the interview study, we will use snowball sampling [41] to recruit more participants. Via snowball sampling, current participants will be asked if they know any other individuals who could participate in the study. As there are no defined rules for calculating sample size in qualitative studies [42], we expect to conduct a minimum of 10–15 interviews minimum with patients with CKD and care providers per group based on previous literature and our experience in previous studies. The definitive sample size for the interviews will be determined based on when data saturation is achieved through the preliminary analysis of the data [43].

#### Outcomes measures & data collection

##### Outcomes for the RCT evaluating the effectiveness

We plan to evaluate:
patients’ physical outcomes including biomedical measures,patients’ lifestyle and psychosocial functioning including self-efficacy, perceptions about CKD, quality of life, anxiety and depression status,hospital admission, health care utilization, and cost-benefit

A trained research assistant will conduct data collection, and the intervention monitoring group will supervise the data collection process. We will invite participants in both the intervention and comparison group to visit the Department of Nephrology at the First Affiliated Hospital of Zhengzhou University for data collection at baseline (T0), 3 months (T1), 6 months (T2) and 9 months (T3) post-randomization. At baseline, we will collect demographic data, including age, race, income, education, marital status, work type of participants. To avoid dropping out of participants, if participants cannot come to the hospital, data will then be collected via telephone interview. Table 6 provides details on the proposed outcome measures and timing of the measures. The operationalization of outcomes and descriptions of the measurement tools used are detailed in Additional file 5.

##### Outcomes for implementation integrity (fidelity), and determinants of implementation

The process evaluation will be based on the RE-AIM framework [67]. The RE-AIM model is used to comprehensively measure the public health impact of research conducted in real-world settings [67]. Four dimensions (with the *Effectiveness* domain being applicable above)—Reach *(refers to the proportion of patients with CKD and care providers reached by our program)*, Adoption *(refers to the proportion of participants who use our intervention)*, Implementation *(refer to completion as well as fidelity to the protocol)*, and Maintenance will be used to evaluate the implementation only in the intervention group. We will collect the implementation outcome measurements throughout the 9-month trial. The outcome measures for each dimension of the RE-AIM model are as described in Table 7.

**Table 7 Tab7:** Implementation outcomes (intervention group only)

Outcome	Outcome Indicators	Measures	Tools	Sources
Reach	Number of patients (eligible, excluded, enrolled)	Records	The proportion of patients eligible to use our intervention program, excluded, invited, and enrolled	Patient
	Number of health care providers (eligible, excluded, enrolled)	Records	The proportion of care professionals eligible to use our intervention program, excluded, invited, and enrolled	Care provider
	Characteristics of participating patients	Records	Comparing participating patients to the target population on key clinical characteristics (e.g., disease stage)	Patient
	Qualitative assessment-reach	Interview	The barriers/facilitators to study participation	Patient
Adoption	Characteristics of participating care providers	Records	Comparing participating care providers to the target population on key characteristics (e.g., work type)	Care provider
	Use of program	Records	Frequency of materials or Medical Dashboard used	Patient, care provider
	Qualitative assessment-adoption	Interview	The appropriateness, comfort, relative advantage, and credibility of the intervention	Patient, care provider
Implementation	Implementation completion	Interview, observation	The implementation completion tasks will be made as a checklist, and the completion of the task and the length of time to finish will be checked.	Patient, care provider
	Acceptability and feasibility of the intervention	Interview	Experiences and perceptions of the intervention	Patients, care provider, research assistant
Maintenance	Follow up on the use of Medical Dashboard	Records	The use of intervention to assess long-term maintenance	Records
	Qualitative assessment-maintenance	Interview	Perceptions of the integration of intervention in health facilities	Patient, care provider

We will use the Measurement Instrument for Determinants of Innovations questionnaire [68, 69] to evaluate the determinants of implementation. Also, individual interviews with stakeholders (e.g. patients, care providers) will be conducted to learn more about the usability and feasibility of Medical Dashboard, its potential for wide-scale implementation, and barriers and facilitators to implementation. We will categorize the determinants identified from this mixed-method study according to Fleuren Framework [70].

### Data analysis

#### Qualitative data analysis

A Framework Method [71] will be used to guide our qualitative analysis. We will structure the qualitative data in a matrix output formed by rows (cases), columns (codes), and ‘cells’ (summarized data). We will follow the Consolidated Criteria for Reporting Qualitative Health Research (COREQ) to ensure quality and validity [72]. The preliminary analysis with proposed codes and a data saturation grid [43] will be performed to determine when data saturation is reached. Also, the codes developed, and results of the preliminary analysis will be taken into account when performing Framework Method analysis.

##### Stage A: transcribing

All audio-taped interviews will be anonymized and transcribed verbatim in Chinese. Long pauses and interruptions (relevant to the study subject) will be noted within the text. Additionally, all participants’ names will be replaced by an ID number. Any names mentioned during the interview will not be transcribed. One researcher will perform transcription, and another will check them to ensure content accuracy.

##### Stage C: development of an analytical framework& coding

Atlas.ti for Windows version 7.5.18 (Scientific Software development, Berlin) will be used to analyze our data. Our study includes four qualitative research parts. These are research into the (1) needs, beliefs, perceptions toward CKD and self-management (phase 1); (2) needs, beliefs, perceptions toward eHealth self-management interventions in CKD (phase 1); (3) the acceptability and usability of intervention components (phase 3); (4) determinants of implementation of eHealth self-management interventions (phase 3). Therefore, based on prior literature in which specific theoretical frameworks were used for similar research questions [73–77], we will develop four distinct initial coding trees. For the first and second research questions, we will develop two coding trees based on the adapted version of the theoretical framework of Brakema et al., (submitted) and the TDF [78]. The Technology Acceptance Model [79] will be used to develop the coding tree for evaluating the acceptability and usability of intervention components. Also, the Fleuren framework [70] will be used to develop the coding tree for determinants of implementation of eHealth self-management interventions. The second researcher and third researcher will check the coding tree developed and make amendments if necessary. One researcher will then independently code two or three transcripts using the coding tree, and add new codes if the textual abstracts identified do not fit with the existing set of codes. Then, this researcher will meet with the second researcher and discuss the newly added codes. New codes will be added into the coding tree, and if needed, related codes will be grouped into categories. Thus, the process will be repeated until no new codes arise.

The final coding tree will be checked and approved by the second researcher and the third researcher. This coding tree will include codes and categories; all codes and categories will be operationalized, and relevant examples will be provided.

The finalized coding tree will then be applied to each transcript. One researcher will go through each transcript, highlight the meaningful textual abstracts, and assign the appropriate code from the final coding tree. Then, all codes assigned will be verified by the second researcher. All coding differences will be discussed until consensus is reached.

##### Stage D: charting data into the framework matrix

Data will be charted into matrices per research question identified by two researchers using Microsoft Excel 2010. The matrix will comprise of one row per participant and one column per code. Interesting or illustrative quotations will be added to the matrices.

##### Stage E: interpreting the data

Overarching themes will be generated from codes derived from the data set by reviewing the matrix and making connections within and between participants and codes. Relations, connections, and causality will be further explored and interpreted, and conclusions will be drawn.

As for data derived from observations, all checklists will be digitalized and transported to Microsoft Excel 2010. Also, all written filed notes will be digitalized and will be taken into account to triangulate data collected from other methods.

#### Quantitative data analysis

All quantitative analyses will be performed using SPSS version 23 (IBM, Armonk, NY, USA). We will enter the quantitative data into Microsoft Excel 2010 and calculate descriptive statistics such as the mean, standard deviation, median, and range of linear variables, and frequencies and percentages of categorical variables.

To gain insight into the needs, beliefs, perceptions of patients with CKD towards disease (self-management) and the use of eHealth interventions in phase 1, we will use the descriptive statistics to describe patients’ demographic characteristics, BIPQ scores, CKD-SM score, and C-eHEALS scores. Also, we will conduct secondary analysis using (1) independent *t*-tests for normally distributed continuous variables, (2) Mann–Whitney U-tests for nonnormally distributed variables and (3) Chi-squared or Fisher’s exact tests for categorical variables to compare the difference between certain types of different groups of patients with CKD (e.g., age, gender, disease stage) and BIPQ scores, CKD SM score and C-eHEALS scores. *P*-values < 0.05 and odds ratios with a 95% confidence interval excluding one will be considered statistically significant.

In phase 3, one of the primary hypothesis is that patients in the intervention group, when compared to the comparison group, will demonstrate (statistically) significant improvement in self-management behavior at 9 months post-randomization. Secondary hypotheses are that the intervention group when compared to patients in the comparison group, will demonstrate (statistically) significant improvement in biomedical status, self-efficacy, illness perception, mental health, quality of life, hospital admission, healthcare utilization and cost-benefit analysis at the timing of measurement. All primary statistical analyses will be conducted using intent-to-treat methods. The primary goal of statistical analyses is to examine and compare trends over time in the primary outcome. We will replicate this analytic approach for other secondary outcomes; secondary analyses will examine trends over time for biomedical status, self-efficacy, illness perception, mental health, quality of life, hospital admission, healthcare utilization, and cost-benefit analysis. We will use longitudinal, mixed-model analyses to test the hypotheses. Exploratory analyses will assess the impact of the intervention on primary and secondary outcomes for patients.

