**Fig. 5 Fig5:**
[figure not shown]
CONSORT flow diagram for our trial

**Table 6 Tab6:** Effectiveness outcomes and timing of measurements

Outcome	Outcome Indicators	Measures	Tools	Sources	Timing of measures			
					T0^**a**^	T1^**b**^	T2^**c**^	T3^**d**^
Primary Outcome	Self-management behavior	Survey	Chronic Kidney Disease Self-Management instrument [38, 56]	Patient	X	X	X	X
Secondary outcome	Biomedical status	Clinical records	Blood pressure, Bodyweight, Glomerular filtration rate, Serum albumin, Length, Serum calcium, Serum phosphate, Serum hemoglobin, Sodium and protein in 24 h urine, albumin/creatinine ratio, Cholesterol, High-density lipoprotein, Low-density lipoprotein, Triglycerides, Hemoglobin A1C, Complications	Patient	X	X	X	X
	Self-efficacy	Survey	Chronic Kidney Disease Self-efficacy scale [56, 59]	Patient	X	X	X	X
	Illness perception	Survey	Brief Illness Perception Questionnaire [37, 60]	Patient	X			X
	Quality of life	Survey	The Kidney Disease Quality of Life 36-item short-form survey [61–63]	Patient	X			X
	Mental health	Survey	Hospital Anxiety and Depression Scale [64]	Patient	X	X		X
	Hospital admission	Survey	The time to first acute hospital admission with an exacerbation of CKD or death due to CKD within 9 months after randomization	Patient				X
	Healthcare utilization	Survey	Number of hospitalizations and emergency room visits of patients, primary and secondary care visits	Patient		X		X
	Cost-benefit analysis	Records	All costs delivering the interventions (e.g., materials used in the interventions)	Program, intervention group		X		X
		Records	Medical cost (e.g., cost of treatment, hospitalization rates minored as monetary terms)	Patient		X		X

^a^At baseline

^b^Three months post-randomization

^c^Six months post-randomization

^d^Nine months post-randomization

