#### Sample size calculation

##### Effectiveness; RCT

Based on previous literature [65], we expect the mean CKD self-management score of patients in the intervention group to be approximately 102 ± 20.53 after the 9-month intervention period. When assuming an 80% power and a two-sided significance level of 0.05, the sample size required in each group is 38 patients [66]. Considering a dropout rate of 30% to follow-up, the sample size of patients in this study needs to be 98 patients in total (49 in the intervention and 49 in the comparison group).

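### Hospital admission is a time-to-first-event outcome recorded once, at T3, but the plan assigns it a longitudinal mixed model of trends over time

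*Protocol article*

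**What the plan says.** Under Quantitative data analysis, the Protocol article sets the comparison of trends over time as the primary statistical goal for self-management behaviour. It continues: "We will replicate this analytic approach for other secondary outcomes". The same sentence then lists the outcomes to be examined for trends, and hospital admission is one of them. The next sentence gives the method: "We will use longitudinal, mixed-model analyses to test the hypotheses". The secondary hypotheses also cover this endpoint, naming "mental health, quality of life, hospital admission, healthcare utilization and cost-benefit analysis at the timing of measurement".

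Table 6 defines the hospital admission outcome as "The time to first acute hospital admission with an exacerbation of CKD or death due to CKD within 9 months after randomization". Its row is marked in one column only, T3, which the footnote gives as "Nine months post-randomization".

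The RCT sample size section expects losses: "Considering a dropout rate of 30% to follow-up". The article names no time-to-event method for phase 3 and makes no exception for this endpoint.

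**The concern.** A model of change over time needs repeated values of the outcome. Hospital admission has one value per patient and no baseline value. It is also a time to event in a fixed window, so it will be incompletely observed in patients who leave early or die of something other than CKD. A mixed model for repeated values has no term for a time known only to exceed the last contact.

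This is not a detail left to an analysis plan. The article gives a method and applies it by name to an outcome that does not fit it. An analysis plan that followed the text would inherit the mismatch. One that departed from it would have to choose a method later, without support from the published protocol. At stake is the one outcome in Table 6 that combines acute admission with CKD death.

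**Working it through.** **Inputs from the Protocol article.** 49 patients per arm and 30% dropout (Sample size calculation, Effectiveness; RCT); a 9-month window and a single recording at T3 (Table 6). The article gives no figure for this endpoint, so there is none to reproduce.

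**Assumptions.** Control risk of 30% at 9 months (range 15–50%), hazard ratio 1 or 0.5, exponential event times, and dropout independent of the event. The article gives only one overall dropout figure, so any split by arm is assumed.

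**Step 1: what the model becomes.** With one row per patient, a random-intercept model has variance σ²(patient) + σ²(residual) for each observation, and only the sum enters the likelihood. In a simulated data set of 98 patients the log-likelihood was −232.174 for every split tried, with the patient share running from 0 to 0.99. The patient effect is not identifiable and there is no time slope. A random effect for care unit could still be fitted, but it would not be longitudinal. What remains is a linear comparison of one observed time per patient.

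**Step 2: the true difference under the assumptions.** Control hazard = −ln(0.70)/9 = 0.0396 per month. Mean event-free time to 9 months is (1 − e^(−9λ))/λ:
- control: 0.300/0.0396 = 7.57 months;
- hazard ratio 0.5: 0.163/0.0198 = 8.24 months;
- difference: +0.67 months.

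**Step 3: three ways of scoring the outcome.** (A) The exit time of a dropout is used as if it were the event time. (B) Only patients who reach T3 are used, and event-free patients are given 9 months. (C) Log-rank with censoring at exit. A and B are compared by t-test, two-sided 5%. There were 6,000 runs per scenario, with exponential dropout times. Where the choice matters for A, figures in brackets are for dropout times uniform over the 9 months.

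| Scenario (dropout control / intervention) | A rejects | B rejects | C rejects |
|---|---|---|---|
| HR 1, none | 5% | 5% | 5% |
| HR 1, 30% / 30% | 5% | 5% | 5% |
| HR 1, 20% / 40% | 26% (21%) | 5% | 5% |
| HR 1, 10% / 50% | 74% (65%) | 5% | 5% |
| HR 0.5, 30% / 30% | 14% | 22% | 31% |
| HR 0.5, 20% / 40% | 8% (7%) | 20% | 31% |

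With HR 0.5, A estimates about +0.52 to +0.55 months under equal dropout and −0.33 (−0.22) under 20% / 40%, the wrong sign. B gives about +0.67 under both, which matches the true value. At 20% / 40% and HR 1, control risks of 15% and 50% give A rejection rates of about 34–35% and 17%.

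**The case against.** The strongest reply is that a linear comparison of this outcome need not be wrong. The endpoint is limited to 9 months, so an event-free patient followed to T3 properly contributes 9 months, and the comparison is then one of restricted mean event-free time. Because Table 6 collects the outcome only at T3, a patient who leaves would most naturally have a missing value (B) and not an exit time scored as an event (A). Under B with non-informative dropout, type I error stays near 5% and the estimate is unbiased, even when dropout differs by arm. The article also plans telephone collection to limit losses. All of this stands. A reader might infer that the prescribed analysis gives an invalid result outright, or that event-free patients have no usable value. The documents support neither reading.

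A reader might also extend the point to healthcare utilisation ("Number of hospitalizations and emergency room visits of patients, primary and secondary care visits") and to costs, as counts and skewed amounts. That does not hold. The article says mixed-model without limiting it to linear models, and generalised mixed models cover such outcomes. Both are marked at T1 and T3, which are repeated measures, and the choice of distribution is commonly left to an analysis plan.

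The reply does not rescue hospital admission. A generalised model still has no trend to fit to a single value and no means of using censored follow-up. B also discards what is known about patients who leave, and a patient who dies of another cause never reaches T3.

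**Conclusion.** The mismatch is real and confined to one secondary outcome; the primary analysis of self-management behaviour is unaffected. The existence of the mismatch needs no assumption, because it follows from setting the analysis text beside Table 6.

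The size of the harm does rest on assumptions, and on a scoring rule that the article does not give. If only T3 completers are used and dropout is unrelated to the event, the cost is power: about 22% against 31% for log-rank at HR 0.5, 30% control risk and 30% dropout in both arms. If exit times stand in for event times, the effect shrinks towards zero under equal dropout, and false rejection reaches about 21–26% at 20% versus 40%. Informative dropout, which was not simulated, could bias either version. Log-rank held its error rate near 5% in every null scenario and had more power than either alternative wherever dropout occurred. Even so, about 31% power means that this endpoint is likely to be inconclusive under any method.

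**What to change.** Under Quantitative data analysis, remove hospital admission from the outcomes analysed for trends by mixed model, and keep that model for outcomes measured repeatedly. State instead that hospital admission will be analysed by a time-to-event method (Kaplan-Meier with log-rank, or Cox regression), with event-free patients censored at 9 months or at last contact if earlier. Add a rule for death from causes other than CKD. Say how provider clustering will be recognised. Study setting lists five sub-units, so a frailty or cluster-robust term should not be relied on without comment on the small number of clusters.

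The cost is wording, plus one small data requirement: event dates and last-contact dates must be recorded for patients who leave before T3, although Table 6 schedules this outcome only at T3. The models for counts and costs need no change on this account.

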#### Design

This study will consist of a 9-month, cluster RCT with two parallel arms, integrated into a hybrid type 2 trial [54]. The trial design and corresponding study elements are detailed in Fig. 4. We selected an intervention duration of 9 months, as previous literature provides support that this intervention duration is sufficient to demonstrate the impact on several self-management outcome indicators [55, 56]. The Standard Protocol Items: Recommendations for Interventional Trials 2013 Statement is used to report the RCT protocol [57] (see Additional file 4), and the Standards for Reporting Implementation Studies will be followed for reporting the implementation study [58].

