A cluster-randomized trial will be performed. This means that health-care providers within different units of the Department of Nephrology will be randomized to either the intervention arm or the control arm using a computer random number generator. Also, we will use block randomization of patients. A biostatistician blind to the study conditions will randomly allocate patients to the intervention (group 1) or control group (group 2) by using a computer-based block randomization procedure. The number of patients in each condition with pre-determined characteristics (i.e., CKD stage, age, gender) will be predefined, and block sizes of 4 and 6 will be used to ensure equal allocation to the two groups. Only the biostatistician will know the block sizes. Thereafter, researchers and patients will be notified of the allocation. The care providers delivering the intervention cannot be blind to the intervention, but will not collect data or analyze outcomes. Those conducting statistical analyses will be blind to group allocation until the evaluation is completed.

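### The trial is labelled cluster randomised, but neither the sample size nor the mixed-model analysis states how the cluster is taken into account

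*Protocol article*

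**What the plan says.** **Design.** Phase 3, Design: "This study will consist of a 9-month, cluster RCT with two parallel arms, integrated into a hybrid type 2 trial". The randomisation text under Study population, recruitment & randomization repeats this ("A cluster-randomized trial will be performed") and says that "health-care providers within different units of the Department of Nephrology will be randomized to either the intervention arm or the control arm".

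**Patient allocation.** The same paragraph goes on to have a biostatistician allocate individual patients to the two groups in blocks of 4 and 6. The numbers per condition with "pre-determined characteristics (i.e., CKD stage, age, gender) will be predefined".

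**Delivery.** Under Intervention, providers in the intervention arm deliver usual care plus Medical Dashboard, and providers in the comparison arm deliver usual care.

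**Sample size.** Expected intervention mean 102 with SD 20.53, 80% power, two-sided 0.05, 38 per group, raised to 49 per group (98 in total) for 30% dropout. No control mean, cluster count, ICC or design effect is given.

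**Measurement.** Patients attend "for data collection at baseline (T0), 3 months (T1), 6 months (T2) and 9 months (T3) post-randomization", and Table 6 marks the primary outcome, the CKD self-management (CKD-SM) score, at all four visits.

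**Analysis.** The hypothesis is that the intervention group "will demonstrate (statistically) significant improvement in self-management behavior at 9 months post-randomization". The text adds: "The primary goal of statistical analyses is to examine and compare trends over time in the primary outcome". The method is one sentence: "We will use longitudinal, mixed-model analyses to test the hypotheses". No model terms are listed.

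**The concern.** In a cluster-randomised trial, patients of the same provider or unit tend to resemble each other, and that shared variation falls wholly within one arm. A test that treats patients as independent then understates the standard error of the arm difference and rejects a true null hypothesis too often.

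A list of covariates or a covariance structure can be left to the SAP. Here the gap is wider. The sample size treats patients as independent, and the only structure that the analysis text names is time. The same omission at both the planning and the analysis stage suggests that the cluster was never carried through from the design label. At stake are the validity of the primary test and the 80% power claim.

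A smaller matter is precision. The role of the T0 score and of the three allocation factors in the model is not stated, and the choice affects power.

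**Working it through.** **1. The plan's own figures.** The 38 per group cannot be derived forwards, because no control mean or difference is stated. Solved backwards with the normal approximation:

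difference = 20.53 × (1.960 + 0.842) × √(2/38) ≈ 13.2, or SMD 0.64.

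With the t-test it is about 13.4, or SMD 0.65. The dropout step is 38 × 1.3 = 49.4, taken as 49. With 30% lost, 49 × 0.7 ≈ 34 per arm remain. No clustering factor is needed to reach these numbers, so none is hidden in them.

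**2. Type I error if clusters are nested in arm and ignored.** Design effect DE = 1 + (m − 1) × ICC; actual error = 2 × [1 − Φ(1.96/√DE)]. There are 68 evaluable patients (34 per arm). The ICC is assumed, because the documents give none. Five clusters means the five sub-units named under Study setting, which is also an assumption; 10 v 10 providers is purely illustrative.

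| Clusters | m | ICC | DE | Error by formula | Simulated t-test |
|---|---|---|---|---|---|
| 2 v 3 | 13.6 | 0.01 | 1.126 | 6.5% | 6.5% |
| 2 v 3 | 13.6 | 0.05 | 1.63 | 12.5% | 13.0% |
| 2 v 3 | 13.6 | 0.10 | 2.26 | 19.2% | 20.3% |
| 10 v 10 | 3.4 | 0.01 | 1.024 | 5.3% | 4.9% |
| 10 v 10 | 3.4 | 0.05 | 1.12 | 6.4% | 6.3% |
| 10 v 10 | 3.4 | 0.10 | 1.24 | 7.8% | 8.1% |

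The simulations are 20,000 runs of a final-score t-test that ignores the cluster.

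**3. Type I error if patients are allocated individually and units treat both arms.** Simulated error without a unit term (10,000 runs, 76 patients, five units): 5.1% at ICC 0.05 and 4.7% at ICC 0.10. There is no inflation.

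**4. Power of a unit-level test.** Five units split 2 v 3 (3 df), 76/5 = 15.2 analysed patients per unit, difference 13.2. The variance of a unit mean is 20.53² × [ICC + (1 − ICC)/15.2], and the standard error of the difference is √[variance × (1/2 + 1/3)].

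- ICC 0.01: power 42.5%
- ICC 0.02: 38.9%
- ICC 0.05: 31.1%
- ICC 0.10: 23.8%

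**5. Role of T0** (34 per arm, SMD 0.65, equal variance at T0 and 9 months, clustering set aside; the correlation r between the two visits is assumed). If T0 is an outcome with free arm means, the 9-month contrast is in effect a change score, with variance factor 2(1 − r). With T0 as a covariate the factor is 1 − r².

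| r | Change factor | Power | Covariate factor | Power |
|---|---|---|---|---|
| 0.3 | 1.40 | 61% | 0.91 | 79% |
| 0.5 | 1.00 | 75% | 0.75 | 86% |
| 0.7 | 0.60 | 93% | 0.51 | 96% |

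**6. Leaving out a balanced allocation factor.** Simulated type I error is 3.8% if the factor explains 10% of the variance and 2.9% if it explains 20% (both assumed). The test becomes conservative.

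**The case against.** The strongest objection is that silence is not exclusion. The analysis sentence lists no terms of any kind, a mixed model can hold a random effect for the unit, and a journal article leaves much to a full protocol or SAP that is not shown. This stands against any claim that the model leaves out the cluster, the baseline or the allocation factors. A reader might infer that from the wording, but the text supports only that they are not stated. The objection does not dispose of the cluster point, because the sample size shows the same gap and there it is visible in the arithmetic.

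Second, the inflation is conditional. The randomisation paragraph describes both provider-level and patient-level allocation. If patients are allocated individually and providers see both arms, the error stays near 5%. That stands. But the Intervention text has each arm's providers deliver that arm's care. On that reading providers are nested in arm even if patients are also allocated individually, and the inflation returns.

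Third, the cluster count is unknown. Five is a description of the department. About 200 providers (60 of them nephrologists) are said to be available, and the number taking part is not given. With many providers and few patients each, the inflation is small.

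Two further readings are tempting and fail. One is that the plan gives up baseline information and rests on a final-score comparison. In fact T0 is a planned repeated measure in a trend analysis, so only its role is open. The other is that ignoring CKD stage, age and gender inflates type I error. It does the reverse.

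**Conclusion.** The point holds as a gap in how clustering is handled. A trial that calls itself cluster randomised states no account of the cluster in its sample size or its analysis, and its two descriptions of allocation leave the randomised unit unclear. The consequence ranges from almost nothing (individual allocation with shared providers, or many small provider clusters at low ICC) to a false-positive rate of about 20% (five units, ICC 0.10). The ICCs and cluster counts are assumptions, and the simulated test is a final-score comparison standing in for a mixed model without a cluster level.

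Restoring the error rate exposes the second half of the problem. With about five clusters, power is well below the stated 80% at every ICC examined. The baseline and allocation-factor points concern precision only and are secondary. Their size rests on an SMD back-solved from 38 per group and on assumed correlations. The change should be made before analysis; it is not shown that the planned analysis is invalid.

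**What to change.** 1. Reconcile the provider-level and patient-level allocation in the randomisation paragraph. State the randomised unit, how many there are per arm, and whether any provider treats patients in both arms.
2. State that the primary mixed model for CKD-SM includes a random effect for that provider or unit and one for patient, with small-sample degrees of freedom.
3. Enter T0 CKD-SM as a covariate, with T1 to T3 as outcomes, and adjust for CKD stage, age and gender. Use the same structure for continuous secondary outcomes that have a T0 value.
4. Restate the power with the assumed ICC, the number of clusters and the target difference. If only about five units are randomised, say plainly that the stated 80% does not apply.

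**Cost.** Analysis wording, plus a provider or unit identifier on each patient record; the other variables are already planned. Intervals will be wider when the ICC is above zero. With about five clusters (3 df), the cluster term protects the error rate but cannot recover the power.
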